## Study management

3

There will be a minimum of two members of the Ethics Committee of West China Jintang Hospital, Sichuan University with no conflict of interest with the study that will make up the Data Monitoring Committee (DMC). The DMC will be responsible for performing routine monitoring and review of studies and reporting to the Ethics Committee to ensure independence from the principal investigator. The DMC can suspend or end the study if they detect any deviation from the approved study protocol or unauthorized modifications in oversight. Every 6 months, reviews will be carried out by the Ethics Committee to check progress against the protocol established. Before trial commencement, the research team will meet with the principal investigator weekly to confirm adherence to protocol standards. Daily communications between the principal investigator and trial manager, with respect to protocol compliance, will be ensured by the trial team, by conducting meetings on a monthly basis during data collection.

Throughout the study, the research team is expected to immediately inform the Ethics Committee in case of any serious adverse event (SAE) or adverse event (AE). If a participant suffers an SAE or AE, regardless of whether it is study-related, the researchers must inform the research team in 24 h and stop the trial. Researchers should stop the trial instantaneously in case of severe errors in programing in the artificial intelligence system or severe issues that are noticed during interaction with users. The research team will then fix the technology and enhance the user interface of the AI system. Once the issues are resolved and checked, the study can be reconstructed and resumed for the sake of participant safety and study validity.

Prior to conducting the study, training sessions and evaluations will be conducted by specialists so that all members of the team are familiar with procedures and technical aspects. To avoid missing follow-ups, we will keep a record of all study participants and link each participant with a distinctive identification number. Further, to make intervention and comparison with the control group consistent, all times for assessments will be the same, and there will be use of similar validated questionnaires. We will have a double data entry and verification process to assure accuracy of the data. Additionally, we will consult statistician experts to determine the most suitable methodologies to use in the study. If we encounter an abnormal data point, we will review the original questionnaires to ensure the accuracy of the data. We will only use data for final analysis after ensuring their absolute accuracy.

The chief researcher will periodically review the work of the research team to ensure adherence to the research protocol and proper data collection procedures. If the research team fails to comply with surveying or follow-up procedures, the chief researcher may take corrective measures, including pausing the trial or altering the randomization scheme. In the event of an issue with questionnaire design or data recording errors, the research team will temporarily halt data collection to address the problem. Any revisions to the questionnaire will be limited to correcting formatting issues, typographical errors, or clarifying wording without altering the underlying constructs or scoring, in order to preserve measurement equivalence. If a substantive change to the questionnaire is deemed necessary, the same revised version will be administered to all affected participants to avoid mixing responses from different versions. Before redistribution, the revised questionnaire will undergo expert review and pilot testing to confirm content equivalence and internal reliability. Once validated, the revised questionnaire will be redistributed to ensure uniformity and reliability of data collection. A data administrator will oversee data management, while a trial administrator will monitor data recording, address issues related to cloud storage and data access, and perform regular checks to confirm that all information is accurate, trustworthy, and compliant with the research protocol.

Unblinding is permitted under this study under special conditions, such as medical emergencies like a serious adverse event or a need for emergency treatment in which knowledge of treatment assignments is urgently required. Participants or their health care providers may also request unblinding after study completion for legitimate medical reasons. To follow these steps for each unblinding request: A written request from the principal investigator or a clinical oversight staff member initiates unblinding. A review panel comprised of clinicians examines each unblinding request for eligibility. Upon approval, members of the study team will disclose group assignments according to the designated protocol in a way that does not pose a threat to study integrity.

All proposed changes to the study will be first brought before the Steering Committee. Once approved, revised content will be submitted to the Hospital Ethics Committee and research department for review and sign-off. Upon approval, there will be a formal document detailing changes made available to all stakeholders, with an electronic copy if required. All changes to the protocol will be recorded by the trial coordinator and signed by the principal investigator. This record will be stored with other trial documents. Once approved by the Ethics Committee, research department, and Ethics Committee, the trial coordinator will modify the clinical trial application.

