#### Withdrawal criteria

2.3.3

Participants who voluntarily request to withdraw from the study for personal reasons, such as scheduling conflicts or changes in interest;Occurrence of severe adverse events during the study, such as serious physical illnesses or acute events (e.g., heart attack, severe infection) that require interruption of the intervention;Changes in medical condition or other medical advice that necessitate altering the original treatment plan, potentially conflicting with the study intervention.

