### Overview of the artificial intelligence system

2.8

“Doubao-pro-32 k,” a Chinese-trained Transformer model optimized for medical knowledge application, was deployed in this study. Doubao-pro-32 k was trained by merging biomedical literature with pain-related clinical guidelines, after which it was fine-tuned on a 32 k context window to produce long-text health education content. Pre-training in general language understanding was carried out on the model before domain-specific fine-tuning to improve medical reasoning ability. Third-party performance benchmarking on the FlagEval evaluation platform^1^ revealed that “Doubao-pro-32 k” scored competitively with GPT-4o. Indeed, overall, “Doubao-pro-32 k” scored 77.75 points, beating GPT-4o’s 73.51 points. Its greatest strength lies in knowledge application (Doubao-pro-32 k: 91.14, GPT-4o: 86.71), an ability that is essential in producing evidence-based clinical information. On development, domain experts performed an initial review of the output from the model to confirm consistency with current medical knowledge and compliance with high levels of medical evidence-based research. Post-pilot study, a sustained validation program will be implemented, such that two experts review 10% of outputs month to month on a back-to-back basis and estimate rates of accuracy to keep system accuracy sustained.

Finally, under this study, maintaining participants’ privacy and securing data integrity in their interaction with the AI-HEALS system are top priority. Any patient data collected through the AI-HEALS system will be held with utmost confidentiality and only for purposes of conducting this study. Each member of our study team is bound by applicable privacy and confidentiality agreements, so both legally and ethically, they are bound to secure participants’ sensitive information. In addition, study participants are entitled to withdraw from participation unconditionally at any point in time without any grounds. This respect for participants’ autonomy guarantees that study members are not pushed to continue. Lastly, all adverse events resulting from intervention will be carefully documented and reported in accordance with local regulations and stipulated procedures.

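### Section 3 orders researchers to stop the trial after any adverse event, however mild or unrelated, which does not fit the participant-level handling set out elsewhere in the protocol

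*Protocol article*

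**What the plan says.** **Section 3, Study management.** The rule for adverse events (AEs) and serious adverse events (SAEs) reads: "If a participant suffers an SAE or AE, regardless of whether it is study-related, the researchers must inform the research team" within 24 hours "and stop the trial". Just before it, the section requires prompt notification of the Ethics Committee for every such event, serious or not.

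The next sentence uses the same phrase for technical faults: "Researchers should stop the trial instantaneously in case of severe errors in programing in the artificial intelligence system". After the technology has been repaired, "Once the issues are resolved and checked, the study can be reconstructed and resumed". That is the only restart text in the paragraph.

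**Section 2.3.3, Withdrawal criteria.** Three grounds for withdrawing a participant are listed:
- the participant's own request;
- "Occurrence of severe adverse events during the study, such as serious physical illnesses or acute events", qualified by "that require interruption of the intervention";
- a change in condition, or medical advice, that makes a different treatment plan necessary and may clash with the intervention.

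**Section 2.8, Overview of the artificial intelligence system.** Here "all adverse events resulting from intervention will be carefully documented and reported in accordance with local regulations". No stop is mentioned.

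**Section 3, unblinding paragraph.** An SAE is a reason to disclose group assignment on request after review, in a way that protects the study's integrity.

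**The concern.** The trigger is any AE. Severity plays no part, and relatedness is expressly set aside. The action is introduced by a word of obligation, so site staff have no discretion under the text.

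The sentence does not say what is stopped. The phrase means the whole study in the sentence that follows, which favours a whole-trial stop. The condition is framed around a single participant, which favours a stop for that person. Neither reading gives a sensible safety rule.

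If the whole trial stops, one minor unrelated complaint in one participant interrupts the study for everyone, and nothing says what must happen before it restarts. If only the participant stops, people leave for events that the AE criterion in Section 2.3.3 would not count. The Introduction itself notes that conventional drug and physical treatments carry adverse effects, so AEs are foreseeable. According to the Trial status section the study began in April 2025, so the rule is in force.

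**Working it through.** **Step 1. Compare the rules.**

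| Place | Trigger | Action | Level |
|---|---|---|---|
| Section 3, AE sentence | Any AE or SAE, related or not | Report and stop | Not stated |
| Section 3, AI-fault sentence | Severe programming error or severe user-interaction problem | Stop, repair, resume | Whole study |
| Section 2.3.3, second criterion | Severe event requiring interruption of the intervention | Withdraw | Participant |
| Section 2.3.3, third criterion | Change in condition or medical advice that forces a new treatment plan | Withdraw | Participant |
| Section 2.8 | AE resulting from the intervention | Document and report | Participant |
| Section 3, unblinding | SAE or other emergency | Disclose assignment, protect integrity | Participant |

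**Step 2. Whole-trial reading.** Section 2.3.3 answers even a severe AE by withdrawing the affected person. The unblinding paragraph protects study integrity after an SAE. Both presuppose that the trial carries on. A halt after every AE does not fit them, and the restart text is tied to repairing the AI system.

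**Step 3. One-participant reading.** The AE sentence stops participation for any event. The AE criterion in Section 2.3.3 needs both severity and a need to interrupt. A mild unrelated event that requires no change of treatment meets the first rule and none of the medical criteria in the second.

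**Step 4. Illustration of how easily the rule is triggered.** The protocol gives no AE rate, so the risk *p* is an assumption throughout.

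The number exposed comes from Section 2.4: 29 per group allowing for 20% attrition is 29/0.8 = 36.25, rounded up to 37, and 2 × 37 = 74. This agrees with the stated total. Observation lasts about 3 + 9 = 12 months per participant.

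With independent participants at equal risk, P(at least one participant has an AE) = 1 − (1 − p)^74, and the expected number of participants with an AE is 74p.

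| Assumed p | P(at least one) | Expected participants |
|---|---|---|
| 0.1% | 1 − 0.999^74 = 7% | 0.07 |
| 0.5% | 1 − 0.995^74 = 31% | 0.37 |
| 1% | 1 − 0.99^74 = 52% | 0.74 |
| 5% | 1 − 0.95^74 = 98% | 3.7 |
| 10% | 1 − 0.90^74 = more than 99.9% | 7.4 |

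The chance passes one half at p = 1 − 0.5^(1/74) = 0.93%. The middle column applies to the whole-trial reading and the last column to the one-participant reading.

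**The case against.** **The two sections are not in strict contradiction.** A reader might infer that staff cannot obey both. The documents do not support that. Section 2.3.3 does not say that its list is exhaustive, and its third criterion can remove someone whose AE is not severe. A whole-trial stop acts at a different level from individual withdrawal. If it is a reversible pause, staff could report, pause, and then withdraw only those who meet Section 2.3.3. Section 2.8 adds a duty to document and report, and forbids nothing. This part of the objection stands. What remains is a poor fit between the rules, and a mandatory instruction with no sensible threshold.

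**The intended meaning may be the milder one.** The wording about a single participant, and the unblinding paragraph, both suggest that the trial continues. That may well be the intent, but the milder reading still removes people for trivial events.

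**The size is unknown.** The illustrated chance runs from 7% to above 99.9% purely on the assumed risk. A reader might also infer lost power or a depleted attrition allowance. Nothing says that an AE stop ends follow-up, and Section 2.13 commits to intention-to-treat with multiple imputation. Even 7.4 losses at an assumed 10% risk would lie within the 74 − 58 = 16 held in reserve, though other dropout would share that margin. No estimate of bias or power loss is justified.

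**Detail may sit elsewhere.** Section 2.8 refers to procedures that are not shown. Those may grade events, but they do not change a sentence that states the wrong rule.

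**Conclusion.** Wrong as written, and worth correcting while the trial runs. Section 3 attaches a mandatory stop to every AE, whatever its severity or cause. On the whole-trial reading this does not fit Section 2.3.3 or the unblinding paragraph, and it has no restart condition. On the one-participant reading it is at odds with the AE criterion in Section 2.3.3. This conclusion rests on the text alone and needs no assumed rate.

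How often the rule would be triggered cannot be stated from the documents. The figures of 52% at 1% risk and 98% at 5% assume independence, equal risk and all 74 participants observed. They show only that a low risk would be enough.

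**What to change.** Delete the stop clause from the AE sentence and write instead:

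> Every AE and SAE, study-related or not, is reported to the research team within 24 h and immediately to the Ethics Committee. The participant's intervention is interrupted, or the participant withdrawn, when any criterion in Section 2.3.3 is met or when the treating clinician judges that safety requires it; follow-up continues where the participant agrees, and other participants continue. A trial-level safety pause is decided by the DMC and Ethics Committee.

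Referring to any criterion in Section 2.3.3 keeps the third one in play. The clinician clause allows interruption for a non-severe but related event. Leave the AI-fault stop rule unchanged.

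The cost is a short amendment by the route in Section 3: Steering Committee, then Ethics Committee and research department. As described, the Data Monitoring Committee (DMC) suspends the study for protocol deviations or unauthorized changes, so its part in a safety pause should be confirmed with it. Reporting stays complete. No new data are needed, and the sample size and analysis do not change.

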### Randomization and blinding

2.2

Randomization in this study is based on a computer-generated random number sequence. Participants will be assigned to intervention and standard care groups at a 1:1 ratio. Randomization will be carried out before patient enrollment so that each patient is assigned to the study’s respective group according to a pre-determined sequence, ensuring randomness and equity. Upon entry, every patient will be given an individual code that corresponds to the random number sequence, with continuous and smooth enrollment. Once randomized, patients will be transferred to an appropriate ward according to their assignment. Intervention group patients, for instance, will be admitted to Ward A, while control patients will be admitted to Ward B to avoid any possible cross-contamination between intervention strategies.

For the purpose of maintaining the confidentiality of the allocation sequence, an impartial team member will conduct the randomization process, who does not engage in participant recruitment nor gets involved in the allocation. This will prevent divulgence of the sequence in the course of the study. The team member will then communicate the allocation outcome to the intervention team, ensuring that neither the participant recruitment team nor the intervention team gains any prior knowledge of the allocation.

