### Informed consent

2.6

The informed consent process will be carried out transparently and openly, with strict adherence to ethical principles. NSLBP patients meeting inclusion and exclusion criteria will be presented with a thorough written explanation of study aims, procedures, possible risks and rewards, and measures to protect patients’ privacy, including meticulous details of collecting, storing, and protecting their information. We will take care to keep all data securely on encrypted computers that only approved study members can access, only for the duration of the study, and will be properly destroyed upon study completion. Individuals will have ample time to read carefully through the consent form, ask questions, and provide consent voluntarily. Participants will be made aware clearly that they can withdraw from study participation at any time without adverse effects. Ongoing consulting contact information will be made available by the study team so that people can seek additional information or explanation at any time. Participants will receive any new information during the study that could influence participation continuation so that ongoing consent is maintained.

In addition, no penalties will be levied upon participants who choose to withdraw from the intervention arm. Patients who withdraw if intervention has already started cannot be reassigned to the control arm and will be counted as natural attrition cases. Where possible, semi-structured interviews with withdrawing participants will be undertaken to examine reasons for departure. Participants will be explicitly made aware of all accessible modes of follow-up in the event of withdrawal through an informed consent process, so that they understand all their rights and options well.

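### The clause letting the chief researcher alter the randomization scheme after missed survey or follow-up procedures conflicts with the pre-determined sequence, is not tied to change control, and should be deleted

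*Protocol article*

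**What the plan says.** The power is in section 3 (Study management) of the protocol article. The trigger is a failure of staff conduct: "If the research team fails to comply with surveying or follow-up procedures". The response follows at once: "the chief researcher may take corrective measures, including pausing the trial or altering the randomization scheme". The section does not say whether the ratio, the list or the method may be altered, or whether the person who alters it must be blind to allocations already made.

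Section 2.2 (Randomization and blinding) describes a fixed, independent process. The ratio is set: "Participants will be assigned to intervention and standard care groups at a 1:1 ratio". The order is set in advance: "Randomization will be carried out before patient enrollment so that each patient is assigned to the study’s respective group according to a pre-determined sequence". Control is kept away from recruiters: "an impartial team member will conduct the randomization process, who does not engage in participant recruitment".

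Section 3 also sets a route for changes: "All proposed changes to the study will be first brought before the Steering Committee". The Hospital Ethics Committee and the research department then review and sign off.

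Section 2.6 (Informed consent) has the only sentence on moving patients between arms, and it is a prohibition: "Patients who withdraw if intervention has already started cannot be reassigned to the control arm and will be counted as natural attrition cases". Section 2.13 (Statistical analysis) states an intention-to-treat analysis.

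**The concern.** The remedy does not fit the fault. If staff miss questionnaires or visits, the data on patients already randomised are incomplete, and changing how later patients are allocated does nothing for those data.

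A sequence protects the comparison because nobody with a view of the trial's progress can influence who goes to which arm. A scheme that one person may alter during the trial, at discretion and for an operational reason, is no longer pre-determined. Two kinds of harm are then possible. If the change lets knowledge of past allocations or of likely next patients shape later assignments, allocation bias follows. If the ratio changes but allocation stays concealed and random, the arms differ in when their patients were recruited, and any trend in outcome over time is confounded with treatment.

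**Working it through.** The point rests on no figure in the plan, so there is nothing to reproduce. The check is to set the passages side by side.

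1. **Trigger against remedy.** The trigger in section 3 is non-compliance with surveying or follow-up procedures. The remedies named are pausing the trial and changing the randomization scheme. Pausing gives time to correct conduct. Changing allocation has no path to completing a missed survey or visit.

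2. **Section 3 against section 2.2 on the sequence.** Section 2.2 says that "each patient is assigned to the study’s respective group according to a pre-determined sequence", at 1:1. Section 3 lets the scheme be altered later. Both cannot hold without a stated exception, and section 2.2 contains none.

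3. **Section 3 against section 2.2 on who controls it.** Section 2.2 gives randomisation to an impartial member outside recruitment. Section 3 gives the power of alteration to the chief researcher and does not mention that member.

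4. **The power against change control, both in section 3.** The approval route covers all proposed changes. The clause grants its power to one person, alongside pausing, with no cross-reference. One reading is that an alteration is a change to the study and needs approval. Another is that an act the protocol already authorises is not a proposed change. The text does not settle which applies.

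5. **Limits on the power.** The same paragraph limits questionnaire revisions closely: formatting, typing errors and clarified wording, with expert review and pilot testing of revised versions. Alteration of the randomization scheme has no comparable limit.

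6. **Visibility of allocation.** Section 2.2 says participants and therapists cannot be fully blinded, and places the arms in separate wards, A and B. The blinding it promises covers the enrolment team, the assistants who collect data, and the analysts. The chief researcher is not listed. The article therefore does not ensure that the person holding the power is unaware of allocations to date.

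7. **Reassignment.** Section 2.6 bars a move to control for those who withdraw once the intervention has begun. Section 2.2 has patients randomised and then transferred to a ward, so some interval, of unstated length, separates randomisation from the start of the intervention. The bar does not mention it. No section permits a move in that interval or at any other time. This is a gap in wording.

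**The case against.** The strongest reply is that the safeguards exist when the article is read as a whole. The approval route in section 3 covers every proposed change, so altering the randomization scheme would need the Steering Committee, the Ethics Committee and the research department. The Data Monitoring Committee may suspend or end the study over deviations or unauthorised modifications. The sequence stays with an impartial member, and the analysis is by intention to treat. On this view only a cross-reference is missing, and the power may never be used.

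Much of this stands. It rules out several stronger conclusions that a reader might draw:

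- *That the randomised comparison is unprotected.* The safeguards above are real. The clause weakens them but does not remove them.
- *That patients may be moved to control.* The only sentence on this is a prohibition, and intention to treat would keep any such patient in the randomised arm for analysis.
- *That the chief researcher runs recruitment.* Section 2.5 gives recruitment to hospital medical staff. Section 3 gives the chief researcher review of protocol adherence and data collection.
- *That no analysis could remove the bias.* A documented, concealed change of ratio leaves allocation random within each period, and adjusting for period deals with it. The statement would fit only selective allocation.
- *That altering the scheme breaches intention to treat.* That principle governs how randomised patients are analysed, not how later patients are assigned.

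The reply does not dispose of the core. Intention to treat cannot protect the assignment of patients not yet randomised. An alteration made under an express power is arguably authorised, so the Data Monitoring Committee's trigger may not apply. Nor would a cross-reference make a changed scheme a sensible answer to missed follow-up.

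**Conclusion.** The concern holds for the clause itself. It is a positive statement in the article, not a detail left to a fuller document. It pairs a data-collection fault with a remedy that cannot help, contradicts the pre-determined 1:1 sequence under independent control, and is not tied to the approval route.

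No size can be given. Any figure would need an assumed change to the scheme and an assumed trend in outcome over time, and the article supplies neither. The consequence is conditional on the power being used, and its kind depends on what is altered: confounding by period if allocation stays concealed and random, allocation bias if it does not. The silence in section 2.6 is a minor point of wording.

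The correction is timely. The Trial status section gives a start in April 2025 and an expected end in December 2026, so the clause may be in force while patients are being randomised.

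**What to change.** 1. In section 3, delete the power to alter the randomization scheme from the list of corrective measures. Keep pausing, and add retraining of staff if wanted.
2. In section 2.2, state that the allocation list is fixed and held by the independent member, and that any change to it may be made only through the Steering Committee, Ethics Committee and research department route in section 3.
3. As a minor clarification in section 2.6, extend the bar on reassignment to the interval between randomisation and the start of the intervention. State that no randomised participant is reassigned at any time and that all are analysed in the arm to which they were randomised.

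This takes a few sentences in one amendment. It changes no procedure that the trial needs, and it has no effect on sample size or on data already collected. If the power has already been used, the date and nature of the change should be recorded so that the analysis can take account of it.
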